### Hypotheses

For the acceptability of the interventions per group, we expect that the ACP intervention with detailed advance treatment orders will be most often acceptable and euthanasia least often acceptable in physicians. No hypotheses on acceptability rated by persons with dementia compared to the other groups are formulated because not enough is known about their views on this matter to formulate specific hypotheses. With regard to acceptability by country, we hypothesize that the ACP intervention with detailed advance treatment orders will be most often acceptable in countries where patients have high autonomy in decision making about medical procedures and care, and where people may feel they need a defence against medical overtreatment, while sanctity of life is not necessarily a dominant principle (in particular, the US). Technology for symptom monitoring when unable to self-report, such as use of cameras in the dying phase, is expected to be most often acceptable in technology-minded countries (Japan, Israel and US). Euthanasia may be most often acceptable in countries that have euthanasia or PAS regulation already in place for a while (in particular the Netherlands and Switzerland) and the least acceptable in countries where ending life is highly controversial (Germany, Israel and Japan).

For the explorative analyses, we expect demographics, variables indicating life view such as religion, view on dementia, attitudes regarding life-prolonging treatment and death and dying, and variables indicating personality such as coping strategy to be associated with acceptability of the interventions. These aspects of life view and personality are selected because they may relate to control. In explaining diversity in acceptability of ACP, individual differences may be more important than differences between countries and respondent groups (hypothesized based on a study in physicians in the UK and the Netherlands; [53]), with those tending to planning as a coping strategy more likely to find the interventions acceptable. Contrary, it could be that people with higher death anxiety are less likely to find the interventions acceptable, as it has been related to fewer preparations for death in people with advanced cancer [54, 55].

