### Sample size calculation

The number of participants is determined by the primary objective of the trial (acceptability). We will use logistic regression analyses and before the COVID-pandemic, we aimed at a total of 6 (countries) x 3 groups) x 50 = 900 respondents for sufficient power according to the 10 events per variable rule of thumb, for a minimum acceptability or non-acceptability rate of 10%. Therefore, with percentages of 10% and up, power would suffice to assess differences between 6 countries and 3 respondent groups. Testing of associations with other characteristics, i.e. life view and demographic and personality characteristics, is exploratory. Also see paragraph ‘Adjustments to protocol’.

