### Secondary study parameters

The secondary outcomes will be assessed using the survey. Table 1 provides an overview of the instruments per group. When not available, the forward-backward translation technique was used to translate the instruments in all languages necessary for the current study (i.e. Dutch, English, German, Japanese and Hebrew). The instruments were translated to each new language by two native speaking researchers independently. They compared their translations and came to a consensus, followed by back-translation by a professional, independent translator. The translation was reviewed by the two researchers and discussed with a third person, the principal investigator or coordinating local partner. The professional translator and original authors were consulted for any remaining specific questions.

To assess attitudes towards the end of life, we use the death anxiety questionnaire [58] as an indicator of a general or global fear of death as a whole. The response options are *strongly disagree* [1], *disagree* [2], *agree* [3] and *strongly agree* [4], and we added *I don’t know* as an additional option. A sum-score can be calculated by summing the scores of the items with a high score reflecting more anxiety about dying. Also, we selected one item of each of the five subscales of the Death Attitude Profile-Revised (DAP-R) [59, 60] to assess attitudes towards death. including: ‘*The prospect of my own death arouses anxiety in me*’ (Fear of death), ‘*I avoid thinking about death altogether*’ (Death Avoidance), ‘*Death is neither good nor bad*’ (Neutral Acceptance), ‘*I look forward to a life after death*’ (Approach Acceptance), and ‘*I see death as a relief from the burden of this life*’ (Escape Acceptance). We will look at the individual items. The seven response categories were reduced to five to match those of the death anxiety questionnaire. Additionally, we use a single item asking the participants about their general level of comfort with talking about the end of life with the response options *very comfortable*, *somewhat comfortable*, *somewhat uncomfortable*, *very uncomfortable*, *don’t know* [11].

To assess caregiver burden, we use the shortened 6-item version of Zarit’s well-tested caregiver burden interview (ZBI-6) [61–65]. Items are scored on a five-point scale, with a cut-off score of ≥ 13 considered as a clinically significant burden [66]. The items are added up to create a sum-score.

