### Data analyses

Descriptive statistics will be used to present the acceptability of the four interventions. The internal consistency of the scales will be calculated using Cronbach’s alpha. Descriptive statistics will be calculated to describe the demographics of the respondent groups per country.

We will use logistic regression analyses with acceptability of the intervention as the dependent variable to examine differences in acceptability between group and countries. ‘*Do not know*’ as a response option is often ignored and excluded from the denominator. A dichotomous variable will be create with a denominator of ‘acceptable versus not acceptable plus do not know’. The analyses will be unadjusted and adjusted for the most important life view or personality parameter (religion for euthanasia, planning for the other interventions). We will explore associations between acceptability and participant characteristics (gender, educational level, age, severity of cognitive impairment for persons with dementia, and palliative care training for physicians) and personality (locus of control, coping), depression, medical decision making, professional or personal experience with dementia, physician’s comfort with end-of-life conversations, and caregiver burden, and life view (religion, death anxiety/attitude, preparedness for end of life, priority quality vs. quantity of life, illness cognition). For this, we will use stepwise backward regression analyses. The analyses will be done with and without adjustment for country and group (forced in the stepwise regression analyses).

Qualitative data from the interviews will be used to map possible ambiguity regarding being in control through the interventions, and as to why and in what situation the participant feels the interventions are acceptable. A content analysis regarding acceptability of the interventions will be conducted. Additionally, across all interviews, we will conduct a thematic analysis on perceptions of control. Data collection and data analysis will be executed iteratively. Coding is supported by the software program ATLAS.ti.

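### Death anxiety carries a directional (exploratory) expectation but is analysed only by backward elimination, so its presence in or absence from the final model is a poor reading of that expectation

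*Protocol article*

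**What the plan says.** The Hypotheses section of the protocol article has a paragraph that opens "For the explorative analyses, we expect demographics, variables indicating life view such as religion, view on dementia". Within it stands a directional expectation: "it could be that people with higher death anxiety are less likely to find the interventions acceptable". The Sample size calculation section gives the status of such tests: "Testing of associations with other characteristics, i.e. life view and demographic and personality characteristics, is exploratory".

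Secondary study parameters describes two sets of measures. One is a death-anxiety questionnaire (four items, per Table 1) that can be summed to a score. For the other, "we selected one item of each of the five subscales of the Death Attitude Profile-Revised (DAP-R", and these five items are to be examined singly. The item for the Fear of death subscale asks about anxiety at the thought of one's own death.

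Data analyses lists the candidates for the exploratory associations, among them "life view (religion, death anxiety/attitude, preparedness for end of life, priority quality vs. quantity of life, illness cognition", and names the method: "For this, we will use stepwise backward regression analyses". Only country and group are forced in. The separate group and country models are "adjusted for the most important life view or personality parameter (religion for euthanasia, planning for the other interventions". Religion and planning therefore also appear in a fixed model, and death anxiety does not.

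**The concern.** Backward elimination answers the question of which subset of candidates survives. The expectation asks something else: in which direction, and how strongly, death anxiety relates to acceptability. When two candidates measure nearly the same thing, each weakens the other's partial test, and which one survives depends heavily on sampling variation. The one that is removed has no odds ratio and no confidence interval in the final model.

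At stake is how the result can be read. Absence of the score from a final model could mean no association, or that a neighbouring item took its place. Survival of any one of several related items is easier to reach by chance than a single planned test.

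**Working it through.** **1. The plan's own figures.** Adjustments to protocol gives 6 countries × 50 physicians = 300, and 7 variables × 10 events = 70 events. Both reproduce. At 50% acceptability, which the article reports for some interventions, there are 300 × 0.5 = 150 responses on each side.

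**2. Which measures overlap.** The Fear of death item and the score measure the same thing. The Death Avoidance item and comfort with end-of-life conversations are related to the score, but are not duplicates. The three acceptance items of the DAP-R concern something else.

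**3. Assumptions not in the article.** Odds ratio 1.5 per SD; p-to-stay 0.05; correlation of 0.5 to 0.7 between score and fear item; two further related items correlated about 0.4; 12 unrelated candidates; joint entry of score and items. Country is forced in. The comparator is a fixed model with country and the score. For scale, at 1,000 simulated data sets a proportion near one half has a standard error of √(0.25/1000) ≈ 1.6 percentage points.

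**4. A true association exists.**
- *The effect acts through the score.* The fixed model detects it in 91-94%, so it misses 6-9%. Elimination keeps the score in about 76-90%, so it drops it in 10-24%.
- *The effect acts through a latent trait that score and items each measure imperfectly.* The fixed model detects it in 65-82%, so it misses 18-35%. Elimination keeps the score in about 30-46%, so it drops it in 54-70%. Some death-related term is nevertheless kept in about 83-93%.

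**5. No association exists (p-to-stay 0.05).**
- One fixed test: about 5%.
- Score or fear item survives: about 10%. Two independent tests would give 1 − 0.95² = 9.8%.
- Any of four related variables survives: about 17-24%. Four independent tests would give 1 − 0.95⁴ = 18.5%.

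The closeness to the independence values shows that most of this is multiplicity over several variables, not an effect of duplication.

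**6. What drives the loss.** A second set of runs put the effect on the score, with log odds ratio 0.34 per SD (odds ratio e^0.34 ≈ 1.40, about 80% power for the fixed model), and used the fear item as the only related candidate.
- Correlation 0.5: the fixed model misses 18.6%; elimination drops the score in 21.5% (21.5/18.6 = 1.16 times).
- Correlation 0.7: 18.6% and 27.6% (1.48 times).
- Correlation 0.8: 20.1% and 30.9% (1.54 times).
- Correlation 0.7 with the fear item left out of the pool: elimination drops the score in 18.2%, the same as the fixed model within simulation error. The loss comes from the overlapping item.
- Correlation 0.7 with score and fear item together in the full model: the score is missed in 47.4%. A fixed model should therefore not contain both.
- p-to-stay 0.10, correlation 0.7: elimination drops the score in 22.4%, against 19.4% missed by a fixed test at 0.05 and 12.0% by a fixed test at 0.10. At correlation 0.5 it drops 15.6%, fewer than the 18.0% missed by the fixed test at 0.05. Under no association, the score or the fear item then survives in 20-21%.

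**The case against.** The strongest reply is that nothing confirmatory is at risk. The expectation stands in a paragraph on explorative analyses, is worded as a possibility, and belongs to tests that the Sample size calculation section calls exploratory. A reader might infer that a formal hypothesis test has been set up to fail. The article does not support that. Nor does it say that survival or removal of a term will be taken as evidence for or against the expectation.

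Second, joint entry of the score and the single items is an inference. The article has one shared candidate entry for anxiety and attitude, and a scoring remark that the DAP-R items are looked at individually. A condensed article can leave that coding to the full protocol. If only one measure enters, displacement does not arise, as the 18.2% above shows.

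Third, only the Fear of death item is a near-duplicate. A reader might treat all DAP-R items as duplicates of the score, but the article assigns each to a different subscale.

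Fourth, under the latent-trait model the construct is usually still found: some related term survives in 83-93%, against 65-82% for the fixed score.

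All four stand, and they limit the point. They do not remove it: an exploratory label does not make selection a good way to read a directional expectation, a dropped term still has no estimate, and the higher survival of some related term comes with a higher chance-survival rate when nothing is there.

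**Conclusion.** The point holds as a weakness in an exploratory analysis. The article states an expected direction for death anxiety and names a method that does not estimate it dependably. If score and items share a pool, the Fear of death item can displace the score. Under the assumptions listed, the score's retention falls from 91-94% to about 76-90%, or from 65-82% to about 30-46%, depending on whether the effect runs through the score or through a shared trait. Chance survival of the score or the fear item is about 10% against 5%.

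A reader might go further and state a single factor of loss, or a 20% chance of retaining a duplicate, as facts about this plan. The documents do not support either. Effect size, correlations and stay level are not given, and the loss ranges from slight to large across plausible values. At p-to-stay 0.05, survival near 20% needs four related variables and is mostly ordinary multiplicity.

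**What to change.** In Data analyses, take the death-anxiety sum-score out of the stepwise pool for this expectation. Fit one prespecified logistic model per intervention: acceptability on country, plus group where groups are pooled, plus the score. Report the odds ratio and confidence interval whatever the p-value. Keep the DAP-R items out of that model and exploratory, and keep the result labelled exploratory.

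The cost is one additional model per intervention on data already being collected. For physicians it has 5 country terms + 1 score = 6 terms, so 6 × 10 = 60 events under the article's own rule, within its 70. With groups pooled it has 5 + 2 + 1 = 8 terms, or 80 events. For interventions that nearly everyone accepts the interval will be wide, which matches the caveat already made in Adjustments to protocol.

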### Data management and monitoring

To protect participant privacy, the data will receive a unique identification code with linkage keys to be stored securely separately from the data. Names and other information that could directly identify the participant are therefore omitted. As long as it is necessary to trace data to an individual participant, the participant identification code list per country will be maintained to enable linking the data to a particular participant. This will be until the data has been fully cleaned and no new cleaning issues have arisen.

Participants can choose to fill in the survey digitally or on paper. We will use a secure certified online program for the digital questionnaires, Castor (Amsterdam, The Netherlands). The data from the paper survey will be entered in the online program by the researcher. We will subject 10% of the data to a random audit by a second researcher to test the accuracy of quantitative data entry of the paper survey and forms. The audio files of the interviews will be deleted after they have been transcribed and the transcripts have been checked. Data will be entered and stored using a secure data server. To allow for cross-national comparison, the study will be performed in non-EU countries according to the same protocol that is acceptable for use in the EU countries.

### Dissemination

The findings will be submitted to relevant peer-reviewed scientific journals and national and international conferences within the field. We will share the results with key stakeholders involved in both homecare and long-term care of persons with dementia to help improve clinical practice. The animation videos are available from the PI upon reasonable request after conclusion of the data collection.

## Discussion

In this study examined the perspectives of persons with dementia, their family caregivers and physicians in six countries (Netherlands, Japan, Israel, US, Germany, Switzerland) to provide insight into the cross-cultural acceptability in dementia care of two ACP approaches, the use of monitoring technology at the end of life, and euthanasia. We anticipated and experienced practical and operational issues in conducting the study. First, due to COVID-19 restrictive measures, more assessments with physicians will be conducted online than initially anticipated. The online assessment offers more flexibility, possibly lowering the threshold for physicians to participate in the study and allowing the research teams to collect data simultaneously in multiple countries. While the COVID-19 pandemic may make it difficult to find physicians who have time to participate in a study, it also highlights the importance of timely ACP and monitoring distress signals at the end of life, possibly motivating physicians to share their opinions about these interventions. Second, we strive to conduct the assessments with the person with dementia and their family caregiver in person. It could be that the person and family caregiver are reluctant to receive visitors, even if allowed. The online option with these groups will also be offered as a last resort option after consultation with the local institutional review board and based on the judgement of the family caregiver if this would be a feasible option for their relative. Third, the recruitment of persons with dementia matching our inclusion criteria may be challenging in countries where dementia is generally diagnosed in a late stage of the disease.

The study limits professional caregivers’ perceptions to those of physicians and nurse practitioners with medical responsibilities whereas nurses have a role in providing these interventions as well. Further, data will not be collected simultaneously in all countries and groups; as a result of the sequential cross-sectional design, we cannot adjust for possible trends over time.

Strengths of this study include the cross-cultural aspect, comparing the perspectives of persons with dementia, family caregivers, and physicians, the sample size, mixed-method design, and initiative to increase the researchers’ transparency and their reflective awareness. The animation videos were developed using input of international experts, have been pilot-tested, and have been reviewed and approved by an independent Ethics Advisory Committee. This study will contribute to a more fundamental understanding of how acceptable a range of interventions differing in level of control offered is, and more generally, as to how and when having control at the end of life in dementia is perceived as beneficial. This facilitates aligning interventions with preferences and will help improve dementia care.

## Abbreviations

ACP: advance care planning
DAP-R: Death Attitude Profile-Revised
ERC: European Research Council
EU: European Union
GP: general practitioner
IE-4: 4-item locus of control scale
IOS: Inclusion of other in the self scale
IPQ-B: Brief Illness Perception Questionnaire
LUMC: Leiden University Medical Center
PAS: physician-assisted suicide
PHQ-2: 2-item Patient Health Questionnaire depression module
QDRS: Quick Dementia Rating System
QUAL-E: Quality at the end of life in terminal patients
US: United States
ZBI-6: Zarit’s caregiver burden interview
